### Statistical analyses

The statistical analyses will be conducted both on a per-protocol (PP) and an intention-to treat (ITT) basis. For PP analysis, all participants who complete the study will be included to evaluate the primary and secondary outcomes. For the ITT analysis, all participants who are enrolled and randomized to one of the two groups and who complete the first visit will be included.

Basic statistics will be reported in terms of mean ± SD for continuous variables, or as percentages for categorical variables. Differences between groups will be analyzed using Student’s *t*-test for continuous variables and the *χ*^2^ test or Fisher’s exact test for categorical variables. The difference in GFR between month 0 and month 12 will be compared between the two groups using Student’s *t*-test for the primary outcome. Analysis of covariance (ANCOVA) will be used to analyze the primary outcome as the secondary analysis to adjust the baseline value. Multivariate Cox proportional hazard regression models will be used to analyze the time to development of anuria. Although the institutions are mainly located in large cities, thereby limiting the likelihood of any important cluster effect, we will be sure to accommodate possible clustering in our models and analysis as required. A value of *P* < 0.05 will be considered statistically significant. All analyses will be performed using SPSS Statistics software (v21.0; IBM Corporation, Armonk, NY, USA).

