### Outcome measures

The primary outcome is the change in GFR between months 0 and 12 after starting treatment. The secondary outcomes will include GFR measured by urine collection, calculated by the mean of the Cr and urea clearance at month 12; time to the anuric state (urine volume <100 ml/day); and fatal and nonfatal cardiovascular events, including acute myocardial infarction, stroke, unstable angina, and cardiovascular revascularization. Parameters obtained by echocardiographic measurements, such as the left ventricular mass index, E/e′ ratio, left ventricular end-diastolic pressure, left ventricular ejection fraction, left atrial volume index, and BP at month 12; parameters measured by BIS, such as the OH value, ECW, and ECW/ICW; hospitalization, cardiovascular and all-cause mortality, and transfer to HD over the course of 1 year; pulse wave velocity (PWV), type and number of PD fluid and diuretics at month 12, and laboratory findings including high-sensitivity C-reactive protein (hs-CRP), N-terminal prohormone of brain natriuretic peptide, and cardiac troponin T, will also be evaluated as tertiary outcomes.

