**Figure 3 Fig3:**
[figure not shown]
**Hypovolemia management flow chart.** APD, automated peritoneal dialysis; CAPD, continuous ambulatory peritoneal dialysis.

Participants who switch to HD or combined dialysis (PD with intermittent HD), receive kidney transplantation, transfer to other institutions, or die during the study will be dropped out of the study. Investigators or research coordinators will evaluate treatment adherence and give scores for each particular item, including 1) percentage of self-reported medical records >80%, 2) percentage receiving PD solutions >80%, 3) adherence to examinations including complete blood count (CBC), chemistry, peritoneal equilibrium test, Kt/V (where K is dialyzer clearance of urea, t is dialysis time, and V is volume of distribution of urea, approximately equal to the patient's total body water), and 4) adherence to the scheduled visits.

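### The per-protocol set of study completers cannot contain fatal cardiovascular events, yet it is used to evaluate that secondary outcome; neither it nor ITT is named as governing

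*Protocol article*

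**What the plan says.** All of this is in the protocol article.

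- **Analysis sets (Statistical analyses).** Two sets are planned: "The statistical analyses will be conducted both on a per-protocol (PP) and an intention-to treat (ITT) basis". The PP set is defined by completion: "For PP analysis, all participants who complete the study will be included to evaluate the primary and secondary outcomes". For ITT, "all participants who are enrolled and randomized to one of the two groups and who complete the first visit will be included". No sentence says which set decides the trial's conclusion. One significance threshold of 0.05 is given for the whole section.
- **Drop-out rule (text after Figure 3, in the section on the physician's treatment guidelines).** Participants who move to HD or combined dialysis, receive a kidney transplant, transfer to another institution "or die during the study will be dropped out of the study".
- **Adherence (same paragraph).** "Investigators or research coordinators will evaluate treatment adherence and give scores for each particular item"; four items are listed.
- **Outcomes (Outcome measures).** The secondary outcomes are month-12 GFR, time to anuria and "fatal and nonfatal cardiovascular events, including acute myocardial infarction, stroke, unstable angina, and cardiovascular revascularization". The tertiary outcomes include "cardiovascular and all-cause mortality, and transfer to HD over the course of 1 year".
- **Timing (Table 1).** Residual renal function and urine volume are scheduled at months 0 and 12 only.

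**The concern.** A set restricted to people who finish the study is selected on what happens after randomization. Here the drop-out rule makes death and departure from PD reasons for not finishing, while death from a cardiovascular cause is also part of a named secondary outcome. The plan thus assigns that outcome to a set that no deceased participant can enter. Protection against cardiovascular events is part of the stated purpose of the trial, so this affects a result that readers will look for.

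Two further features add to the problem. The set is called per-protocol but, as worded, does not depend on adherence. A poorly adherent participant who reaches month 12 is in, and a fully adherent one who is transplanted or dies is out. And the hypothesis is one of superiority in an open-label trial, where it matters which set carries the conclusion if the two disagree.

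**Working it through.** **1. The plan's own numbers.** From Sample size calculations: changes of -16.8 ± 19.9 and 0.09 ± 40.9 l/week/1.73 m², two-sided α of 5%, power 80%, drop-out 20%.

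- Difference: 0.09 - (-16.8) = 16.89.
- Pooled SD: √[(19.9² + 40.9²)/2] = 32.16.
- n per arm: 2 × (1.960 + 0.842)² × 32.16² / 16.89² = 56.9, so 57.
- 57 × 1.2 = 68.4, rounded up to 69 per arm and 138 in total. This is the stated figure. (Dividing by 0.8 would give 71.25, so 72; that is a side point.)

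**2. How many participants fall outside PP.** At the planned drop-out, 138 × 0.8 = 110.4 complete, about 55 per arm. 138 × 0.2 = 27.6, about 28 people, do not. The article does not say how many of these would be deaths or HD transfers.

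**3. What a completer set can contain.** Setting the drop-out rule beside the PP definition and the outcome list:

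| Outcome | Tier | In PP as worded |
|---|---|---|
| Fatal cardiovascular events | Secondary | 0 in each arm, by construction |
| Nonfatal cardiovascular events | Secondary | Counted, but only in people who finish |
| Time to anuria | Secondary | People who later die, leave PD or transfer are absent altogether |
| Mortality, transfer to HD | Tertiary | 0 in each arm, if PP is extended to tertiary outcomes |

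**4. Time to anuria.** A Cox model handles someone who leaves early by censoring at exit, with any earlier anuria counted as an event. The completer set deletes the whole record instead. Someone who becomes anuric and then moves to HD disappears together with the event. Loss of residual function may itself be related to leaving PD, so the deletion cannot be assumed unrelated to the outcome. How many events this loses depends on how urine volume is captured between visits, since Table 1 schedules it only at months 0 and 12.

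**5. Primary outcome.** The t-test on the change from month 0 to month 12 needs both GFR values. If drop-outs have no month-12 value and none is imputed, the ITT test and the PP test both run on about 110 participants. Comparing the two would then say almost nothing about sensitivity to drop-out. At 55 per arm, power under the plan's assumptions is 78.6% by the normal approximation, or 77.9% by the t-test. If missing values were imputed, ITT could hold up to 138 against about 110 in PP, and the sets would differ.

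**The case against.** The strongest reply is that the defect sits in a second analysis set. ITT is also planned and, as defined, includes participants who die, so fatal events are not lost to the trial. Nonfatal infarction, stroke, unstable angina and revascularization in completers are still counted in PP. That is right, and it limits the point to the fatal component and to selection in the rest. A reader might go further and call all PP event results meaningless; the text does not support that.

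Other stronger readings also fail:

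- *That ITT and PP are the same people for the primary outcome.* The article defines two different sets. They coincide only without imputation. The article gives no missing-data rule, which may properly sit in a plan not shown, and its statement that all 138 will be in the analysis fits poorly with a complete-case reading.
- *That HD transfer is certainly zero in a planned PP analysis.* HD transfer is tertiary, and the PP sentence names only primary and secondary outcomes. The zero follows only if the general sentence on both bases reaches the tertiary tier.
- *That the plan declares PP and ITT equal in rank.* It leaves them unranked, which is weaker.

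It may also be said that adherence could enter through the meaning of completing the study, because the sample size section attributes drop-out to poor compliance. But the listed drop-out reasons do not include poor compliance, and the PP sentence uses none of the scores. A full protocol might settle this; the published sentence does not.

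The first-visit condition in the ITT definition is a minor matter. A participant with no month-0 visit has no baseline GFR, and no number excluded can be given. The point does not rest on it.

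**Conclusion.** The concern stands in a limited form. It follows from three statements in the article: the PP set is made up of completers, death and leaving PD are drop-outs, and fatal cardiovascular events are a secondary outcome. Together they make fatal events exactly zero in both PP arms, and they remove people from PP time to anuria because of their later status. The logic needs no assumption about event rates. The practical size does: the article gives no expected number of deaths, and only the planned total of about 28 non-completers can be stated.

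Two weaker parts also hold. The PP definition as worded does not use adherence, and no set is named as governing. The overlap of the ITT and PP tests on GFR, about 110 of 138, is conditional on 20% drop-out, no month-12 GFR in drop-outs, and no imputation.

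**What to change.** Change the wording in Statistical analyses:

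- Name ITT, meaning randomized participants by assigned arm, as the governing analysis for all outcomes.
- Count events up to exit, and censor participants who leave early at exit in the time-to-event analyses.
- Define PP by the adherence items already scored, and limit it to a supportive analysis of GFR.
- Do no PP analysis of cardiovascular events, time to anuria, mortality or HD transfer.
- Say how a missing month-12 GFR is handled in ITT, or refer to the document that does. The choice of method need not be settled for this point; with no GFR scheduled between months 0 and 12, any imputation would have little to draw on.

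The change of wording needs no new data. PP results would no longer be reported for event outcomes. Events after drop-out stay unobserved, in ITT as well, unless follow-up continues after participants leave PD or the center. Continuing it would be an added cost.

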### Clinical and laboratory evaluations

Physical examination, medication reviews including PD solutions, fluid balance evaluation (semi-quantitative scale),. and laboratory evaluations, including CBC, electrolytes, Cr, protein, albumin, calcium, phosphorous, and fasting glucose will be conducted every 2 months.

Laboratory evaluations, including total cholesterol, triglyceride, low-density lipoprotein cholesterol, hs-CRP, hemoglobin A1C, intact parathyroid hormone, N-terminal prohormone of brain natriuretic peptide, cardiac troponin T, and weekly Kt/V_urea_, will be performed at months 0 and 12 of treatment. Echocardiography will be performed, and PWV will be measured using a Colin pulse waveform analyzer (Colin CO, Ltd, Komaki, Japan) at months 0 and 12 after treatment. The study schedule is shown in Table 
1.

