### Sample size calculations

No previous report has evaluated the effect of BIS-guided fluid management on RRF in patients on PD. We therefore referred to a study showing that GFR changes over 1 year in a conventional PD solution treatment group and in a biocompatible PD solution treatment group were -16.8 ± 19.9 and 0.09 ± 40.9 l/week/1.73 m^2^, respectively
[13]. We adjusted the sample size for an estimated drop-out rate of 20% due to poor compliance, a two-sided level of significance of α = 5%, and a power of 80%, and found that 69 participants will be required in each group to find a significant difference using Student’s *t*-test. A total of 138 participants will be included in the analysis.

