[23–25]. Although some studies have suggested cutoff thresholds for the definition of the OH in patients on HD and patients on PD of 2.5 and 2.0 liters, respectively
[19, 26, 27], we consider an ECW within ±1.1 liter as normal hydration.

There is a chance that patients within the same institution will be more correlated than patients between institutions. To avoid this, we will investigate for possible clustering of patients at the recruitment institution level, and will accommodate such clustering in our models and analysis as required. We also conservatively calculate the sample size, assuming a high drop-out rate, to overcome this potential problem.

A limitation of this study is that we will include both prevalent and incident patients on PD. Although a study targeting only incident patients on PD might provide more solid results, we will adjust the dialysis vintage in the multivariable analyses.

In summary, the COMPASS study is the first prospective, randomized controlled trial to evaluate the clinical usefulness of BIS-guided fluid management in patients on PD. The aim of this study is to evaluate whether BIS-guided fluid management has a beneficial effect on the decline of RRF, cardiac parameters, and cardiovascular outcomes.

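### Tertiary continuous outcomes have no stated baseline adjustment and no provision for skewed markers, so their comparisons may be less precise than the collected data allow (minor)

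*Protocol article*

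**What the plan says.** The Statistical analyses section of the protocol article gives a single descriptive rule, "Basic statistics will be reported in terms of mean ± SD for continuous variables", and a single comparative one: "Differences between groups will be analyzed using" Student's t-test when the variable is continuous. Neither depends on the shape of the distribution. No log scale, median or rank test is mentioned.

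Baseline adjustment appears once, for GFR: "Analysis of covariance (ANCOVA) will be used to analyze the primary outcome as the secondary analysis to adjust the baseline value". The Discussion adds one other covariate, "we will adjust the dialysis vintage in the multivariable analyses", which is not the baseline value of the outcome.

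The Outcome measures section lists "laboratory findings including high-sensitivity C-reactive protein (hs-CRP), N-terminal prohormone of brain natriuretic peptide, and cardiac troponin T" together with echocardiographic, blood pressure, pulse wave velocity and bioimpedance parameters, and says these "will also be evaluated as tertiary outcomes". Under Clinical and laboratory evaluations, the three markers "will be performed at months 0 and 12 of treatment". Table 1 schedules echocardiography, pulse wave velocity, blood pressure and, in both arms, the body composition measurement at the same two visits. A month-0 value is therefore planned for each of these outcomes.

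**The concern.** Two features of the general rule fit these outcomes poorly.

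- **Baseline.** Where an outcome correlates with its own month-0 value, ANCOVA removes that share of the variance. The plan does this for GFR but does not state it for the other outcomes with the same two measurements.
- **Scale.** hs-CRP, NT-proBNP and troponin T are concentrations bounded at zero and plausibly right-skewed. With strong skew, a few high values dominate the mean and SD. The summary then describes patients badly and the standard error of the t-test is inflated.

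The Discussion includes cardiac parameters in the aim of the study, and several of these outcomes bear on it. The sample size is set for GFR alone. A non-significant tertiary result from an inefficient analysis could be misread as absence of a cardiac effect.

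**Working it through.** **What the plan itself computes.** It gives no power, SD or effect for any tertiary outcome. Its only figure is for GFR change: difference 0.09 + 16.8 = 16.89, pooled SD √((19.9² + 40.9²)/2) = 32.16, which gives 57 per group; 57 × 1.2 = 68.4, so 69. That reproduces the stated size but does not bear on this point. It is used only to set n: 69 × 0.8 ≈ 55 per arm with a month-12 value.

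**Step 1: baseline adjustment, any continuous outcome.** Assume equal variance σ² at both visits and correlation ρ between them. The variance of the arm difference, in units of 2σ²/n, is:
- month-12 t-test: 1
- t-test on change: 2(1 − ρ)
- ANCOVA: 1 − ρ² (ignoring the small cost of estimating the slope)

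| ρ | Month 12 | Change | ANCOVA |
|---|---|---|---|
| 0.3 | 1 | 1.40 | 0.91 |
| 0.5 | 1 | 1.00 | 0.75 |
| 0.7 | 1 | 0.60 | 0.51 |

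Since 1 − ρ² ≤ 1 and 1 − ρ² = (1 − ρ)(1 + ρ) ≤ 2(1 − ρ), ANCOVA is at least as precise as either version of the t-test. At ρ = 0.5 its interval is √0.75 = 0.87 times as wide as both.

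**Step 2: what skew does to mean ± SD.** For a lognormal marker with log-scale SD s, SD/mean = √(exp(s²) − 1). This is √0.284 = 0.53 at s = 0.5, √1.718 = 1.31 at s = 1.0 and √4.42 = 2.10 at s = 1.3. In the last two cases mean − SD is negative, which a concentration cannot be.

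**Step 3: power for the three markers.** Simulation with 10,000 trials per setting, 55 per arm, two-sided 5%. Assumed inputs, none from the documents: lognormal marker, s of 0.5, 1.0 or 1.3, log-scale correlation 0.3 to 0.7, true ratio of geometric means 0.7 or 0.6. Strata were not modelled. Selected results (power, %):

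| s | ρ | Ratio | Raw t, month 12 | Raw t, change | Raw ANCOVA | Log t | Log ANCOVA |
|---|---|---|---|---|---|---|---|
| 0.5 | 0.3 | 0.7 | 93.6 | 74.4 | 95.0 | 95.7 | 97.1 |
| 0.5 | 0.5 | 0.7 | 93.9 | 86.0 | 97.7 | 96.2 | 99.0 |
| 0.5 | 0.7 | 0.7 | 93.3 | 97.1 | 99.8 | 96.0 | 100 |
| 1.0 | 0.3 | 0.7 | 31.2 | 18.9 | 32.7 | 45.2 | 48.4 |
| 1.0 | 0.5 | 0.7 | 32.7 | 23.5 | 37.7 | 46.9 | 57.5 |
| 1.0 | 0.7 | 0.6 | 56.9 | 53.2 | 75.5 | 76.1 | 96.0 |
| 1.3 | 0.3 | 0.7 | 16.5 | 10.3 | 17.0 | 30.1 | 31.9 |
| 1.3 | 0.5 | 0.6 | 30.0 | 19.1 | 34.0 | 53.4 | 64.7 |
| 1.3 | 0.7 | 0.6 | 29.8 | 26.9 | 43.1 | 53.2 | 81.5 |

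Over all settings with s of 1.0 or 1.3, log-scale ANCOVA exceeds the raw month-12 t-test by 31.9 − 16.5 = 15.4 to 81.5 − 29.8 = 51.7 points. At s = 0.5 the gap is at most 100 − 93.3 = 6.7 points.

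**Hand check.** For s = 1.0, ratio 0.7, the log t-test has SE √(2/55) = 0.191 and |ln 0.7|/SE = 1.87, so power is Φ(1.87 − 1.96) = 46%. With ANCOVA at ρ = 0.5, SE is 0.191 × √0.75 = 0.165, the ratio is 2.16 and power is Φ(0.20) = 58%. Both agree with the table.

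**Type I error.** With a true ratio of 1, the raw month-12 t-test rejected in 3.5% to 4.9% of trials over all settings (55 and 69 per arm).

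**The case against.** The strongest reply is that this is a short general rule in a condensed article. It does not say raw scale, does not forbid transformation, and a t-test on log values is still Student's t-test. A full analysis plan may deal with skewed tertiary laboratory values. The markers are tertiary, no power is claimed for them, and nothing in the article describes their distribution.

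Much of this stands, and it rules out three stronger readings that a reader might infer:

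- **That the trial will lose much of its power on these markers.** The documents give no skew, effect size or correlation. The loss against the month-12 t-test runs from a few points to about 50 depending on assumed values.
- **That the plan discards the month-0 values.** The text does not say whether the tertiary t-test uses the month-12 value or the change. For GFR it is applied to the change, so that is not excluded here.
- **That the tests are invalid.** Type I error is not inflated in the simulation, and GFR already has a baseline-adjusted analysis.

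The reply does not remove the point. The article states a rule rather than leaving one open, and confines ANCOVA to GFR. Reading the test as one on change does not help: in the strongly skewed settings that test is worse than the month-12 test at correlations 0.3 and 0.5 and roughly level at 0.7. Even at log-scale SD 0.5 it falls 97.1 − 74.4 = 22.7 points short of log-scale ANCOVA when the correlation is 0.3.

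**Conclusion.** The point holds as a minor matter of efficiency and description. The article names no baseline adjustment for tertiary outcomes that have both a month-0 and a month-12 value. Given any correlation between the visits, either version of the t-test is less precise than ANCOVA, except that the change score approaches it as the correlation nears 1. This part rests only on equal variance at the two visits.

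The further loss for hs-CRP, NT-proBNP and troponin T is conditional. It is roughly 15 to 50 points of power against the month-12 t-test if the log-scale SD is about 1.0 to 1.3, and at most about 7 points if it is 0.5. It assumes a lognormal marker, a multiplicative effect (ratio 0.6 to 0.7), correlations of 0.3 to 0.7 and 55 per arm. No skewness is alleged for the echocardiographic, pulse wave velocity, blood pressure or bioimpedance outcomes; for them only the baseline argument applies. The primary analysis and sample size are not affected.

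**What to change.** In Statistical analyses, state that each continuous tertiary outcome with month-0 and month-12 values is analysed by ANCOVA on the month-12 value, with arm, the month-0 value and the randomisation strata (institution, diabetes) in the model. For hs-CRP, NT-proBNP and troponin T, fit this model on the log scale, report the ratio of geometric means with its 95% CI, and summarise each arm by median (IQR).

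The cost is wording only: no extra visit, assay or participant. The downside is that for these three markers the estimand becomes a ratio of geometric means instead of a difference in means, which should be said in the text. The article reports recruitment as ongoing, so the choice can be fixed before the month-12 results are analysed and will not look data-driven.

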### Randomization

The randomization process will be conducted using a web-based computer program. A list of random numbers will be generated by a computerized random allocation system operated by the Medical Statistics Support Team in Seoul National University Hospital. Eligible participants will be randomly assigned 1:1 to either the control group (fluid management based on the clinical information alone) or treatment group (BIS-guided fluid management along with clinical information). Randomization will be stratified based on the institution and presence of diabetes mellitus, and will utilize a randomized block design.

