**Table 1 Tab1:** **Data collection schedule of the COMPASS study**

Parameter	Visit time (months)							
	-1	0	2	4	6	8	10	12
Demographic information	X							
Charlson Comorbidity Index	X							
Physical examination^1^	X	X	X	X	X	X	X	X
Medication review^2^	X	X	X	X	X	X	X	X
Routine laboratory data^3^		X	X	X	X	X	X	X
Special laboratory data^4^		X						X
RRF, urine volume		X						X
Compliance		X	X	X	X	X	X	X
New events^5^		X	X	X	X	X	X	X
BCM measurement								
Treatment group		X	X	X	X	X	X	X
Control group		X						X
Kt/V		X						X
Peritoneal equilibration test		X						
PWV		X						X
Echocardiography		X						X
PD solution, medication change		X	X	X	X	X	X	X

BCM*,* Body composition monitoring; COMPASS*,* Control Of fluid balance guided by body composition Monitoring in patients on PeritoneAl dialySiS trial; Kt/V*,* Calculated using single pool equation; PD*,* Peritoneal dialysis; PWV*,* Pulse wave velocity; RRF*,* Residual renal function.

^1^Includes body weight with an empty abdomen, blood pressure, pulse rate, and edema.

^2^Number of anti-hypertensive medications and diuretics and the type of PD solution.

^3^Complete blood count, electrolyte, serum creatinine, protein, albumin, calcium, phosphorous, and fasting glucose.

^4^Total cholesterol, triglyceride, low-density lipoprotein cholesterol, high-sensitivity C-reactive protein, hemoglobin A1C, intact parathyroid hormone, N-terminal prohormone of brain natriuretic peptide, and cardiac troponin T.

^5^Any new clinical event, including hospitalization and peritonitis, will be recorded during the study period.

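### The only stated test that fits cardiovascular events and hospitalization ignores follow-up time, although participants leave early, and the completers-only set cannot contain deaths or HD transfers

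*Protocol article*

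**What the plan says.** All places are in the Protocol article.

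- **Statistical analyses.** Group differences are tested by Student's t-test if continuous and by chi-square or Fisher's "exact test for categorical variables". Named exceptions follow: ANCOVA as a secondary analysis of the primary outcome, and Cox "regression models will be used to analyze the time to development of anuria". Two analysis sets are defined. PP takes those who complete the study, and is to be used for primary and secondary outcomes. ITT takes everyone randomized who completes the first visit.
- **Outcome measures.** Fatal and nonfatal cardiovascular events are a secondary outcome. The tertiary outcomes include "hospitalization, cardiovascular and all-cause mortality, and transfer to HD over the course of 1 year". None of these is defined as a time to event.
- **Paragraph after the Figure 3 legend.** Participants who switch to HD or combined dialysis, receive a transplant, "transfer to other institutions, or die during the study will be dropped out of the study".
- **Table 1, footnote 5.** "Any new clinical event, including hospitalization and peritonitis, will be recorded during the study period". The new-events row is marked at every visit from month 0 to month 12.
- **Sample size calculations.** Drop-out of 20% is expected, attributed to poor compliance, with no split by arm.

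**The concern.** Protection against cardiovascular events is part of the purpose stated in the Background. A comparison of 12-month proportions is sound when everyone is observed for 12 months. Here some participants are not, by design. Someone who leaves at month 2 without an event contributes two months of information, but a chi-square test on the ITT set takes it as twelve event-free months. Absolute risks are then understated in both arms. If exits differ between arms, the comparison tilts towards the arm with more or earlier exits. Exits could differ, because HD transfer is both a reason for exit and an outcome that the intervention might change.

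The PP set has a different fault. Death and HD switch end participation, so nobody who completes the study can have had either. A PP analysis of cardiovascular events, which the plan calls for, leaves out every fatal event and every nonfatal event in a person who later left.

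**Working it through.** **1. The plan's own figure.** No figure is given for the event outcomes, so only the group size can be reproduced. Inputs from Sample size calculations: mean changes of −16.8 (SD 19.9) and 0.09 (SD 40.9), two-sided α of 5%, power of 80%.

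- Difference = 16.8 + 0.09 = 16.89
- SD = √[(19.9² + 40.9²)/2] = 32.16
- n = 2(1.960 + 0.842)² × 32.16²/16.89² = 56.9, so 57 per group
- 57 × 1.2 = 68.4, so 69 per group, as stated

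How drop-out was added is a separate matter. Only the 69 per arm is used below.

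**2. Undercount in the ITT set.** Assumptions: constant event hazard, exits spread evenly over 12 months and unrelated to event risk, leavers without a recorded event counted as event-free. With true 12-month risk p, h = −ln(1 − p), and exit proportion d:

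observed risk = (1 − d)p + d × [1 − p/h]

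The bracket is the mean risk accrued before exit. For p = 0.05, h = 0.0513 and the bracket is 0.0252. At d = 0.20:

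0.80 × 0.05 + 0.20 × 0.0252 = 0.0450

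So 5% appears as 4.5%, and about 10% of events are missed. The 20% is the plan's drop-out figure; applying it to these exits is an assumption.

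**3. Ratio between arms when the true risks are equal.** The ratio is the arm with more exits over the arm with fewer.

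| True risk | 20% v 20% | 15% v 25% | 10% v 30% |
|---|---|---|---|
| 5% | 1.00 | 0.0438/0.0463 = 0.95 | 0.0426/0.0475 = 0.90 |
| 10% | 1.00 | 0.0877/0.0926 = 0.95 | 0.0853/0.0951 = 0.90 |
| 40% | 1.00 | 0.3542/0.3725 = 0.95 | 0.3451/0.3817 = 0.90 |

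The event risks and the splits by arm are assumptions, since the documents give neither.

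**4. A second exit model.** With exponential drop-out at rate μ and event hazard λ, observed risk = λ/(λ + μ) × [1 − exp(−(λ + μ))]. For risks of 5% to 30%, the ratio is 1.00 at equal drop-out, about 0.94 at 15% v 25% and about 0.89 at 10% v 30%. The actual size of a nominal 5% two-proportion test at 69 per arm is then 0.050, 0.051–0.055 and 0.053–0.069.

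**5. Bias beside imprecision.** At a 5% risk, 69 × 0.05 = 3.45 events are expected per arm. The standard error of the log risk ratio is √[2 × (1/3.45 − 1/69)] = 0.74. The bias on the same scale is ln 0.95 ≈ −0.05 or ln 0.90 ≈ −0.11.

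**6. The PP set.** No arithmetic is needed. Death and HD switch are reasons for drop-out and PP requires completion, so the PP count of fatal cardiovascular events, deaths and HD transfers is zero in both arms whatever happens.

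**The case against.** The strongest objection is that no sentence assigns chi-square or Fisher to these outcomes by name. The rule is general, it follows the remark on descriptive statistics, and a condensed article may leave outcome-specific methods to a fuller document. That stands as a limit: the assignment is an inference. It is a short one, because the section states a blanket rule and then lists exceptions, and these outcomes are not among them.

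A reader might go further and infer that the plan counts unobserved time as event-free for all four kinds of event, and so biases the comparison. The documents do not support that, for four reasons.

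- They do not say how an early leaver is coded. The mechanism arises only in the ITT set, and only if a simple proportion is used there. In PP the leavers are absent.
- Death and HD switch are themselves reasons for exit, so they are recorded when they cause it. What can be lost is a later event, such as death after transplant. The mechanism applies mainly to cardiovascular events and hospitalization.
- Bias in the ratio needs unequal exits or exits related to risk. No split by arm is given, and with equal exits under the assumptions above the ratio is 1.00.
- Even with unequal exits, the bias is small beside the imprecision at 69 per arm.

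The scheduling of urine volume only at months 0 and 12 bears on the anuria analysis. It adds nothing to this point.

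It can also be said that censoring in a Cox model does not cure exits related to risk. That is right, and the fix therefore has to state the assumption.

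**Conclusion.** The point holds in a limited form. For cardiovascular events and hospitalization, the only stated method that fits takes no account of follow-up time, while the plan removes participants early and reviews new events every two months, which would support a better method. In the ITT set, a simple proportion would understate risk by about 10% at 20% drop-out. It would shift the ratio to about 0.95 or 0.90 only under the assumed splits of 15% v 25% or 10% v 30%, and not at all if exits are equal and unrelated to risk. The fault in the PP set needs no such assumption: completers cannot include fatal cardiovascular events, deaths or HD transfers. The outcomes affected are secondary and tertiary. The primary GFR comparison and the stated sample size do not change.

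**What to change.** In Statistical analyses, after the sentence on anuria, add the following.

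- **Cardiovascular events and first hospitalization:** analyse in the ITT set as time from randomization to first event, with cumulative-incidence curves and a cause-specific Cox model. Stratify or adjust for diabetes and, where event numbers allow, institution, since both are stratification factors. Treat death that is not part of the endpoint as a competing event. Count events after HD transfer or transplant where they are known; otherwise censor at last contact and state that this assumes non-informative censoring.
- **All-cause death:** Kaplan-Meier curves and a Cox model, with no competing event.
- **Transfer to HD:** the same approach as for the first item, with death and transplant as competing events.
- **Analysis set:** do not use the completers-only PP set for these event outcomes.
- **Chi-square and Fisher tests:** keep them for categorical outcomes observed at one time point in everyone analysed.

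Cost: revised wording, a little more analysis work, and use of event and last-contact dates from the two-monthly review. No visits or participants are added. Events will be few, so estimates will stay imprecise whichever method is used.
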